### Sample size for the qualitative study

We do not know in advance how many interviews will be necessary to reach saturation (with no new themes emerging), but we will plan to interview ten dyads of participants with Down syndrome and their caregivers and will also attempt to recruit ten dyads of adults with Down syndrome and their caregivers who choose not to participate in the pilot RCT. It is possible that some dyads will agree to this single, semistructured interview despite having declined to participate in the pilot RCT.

### Participants and their recruitment

For the RCT, we will recruit approximately 60 adults with Down syndrome ages 50 and older. Potential participants will be given or sent information packs and invited to reply to the research team if they are interested in further information about participating.

Although all older adults with Down syndrome will be known to their primary care teams, it is likely that a more efficient recruitment strategy will combine primary care, registry-based and wider recruitment methods, with snow-balling. We will test recruitment using a multipronged approach in Greater Glasgow and Clyde, Lothian and Tayside utilizing the following resources:

1. Scottish Primary Care Research Network

2. Scottish Dementia Clinical Research Network

3. Down Syndrome Scotland membership list

4. Scottish Consortium for Learning Disabilities and their e-SAY project

5. Professionals working within specialist intellectual disabilities health and social work services

6. Larger provider organizations of 24-hour support packages and specialist day care

If the recruitment rate is lower than anticipated within the first 2 months of recruitment initiation, then approvals will be sought to expand recruitment efforts into other areas of Scotland utilizing the same methods. If interest to participate in the study is high, we will recruit the first 60 suitable participants while continuing to measure the response rate. To judge the most effective means of recruitment, during the screening call to gauge each individual’s eligibility to participate in the study, we will inquire if the person knows the source of the information pack they received which resulted in their replying for more information about the study.

Two groups of participants will be selected for the qualitative study. They will be drawn from among (1) those who participated in the RCT and (2) those who declined to participate in the RCT or did not respond to the invitation to participate. For the first group, we will try to avoid bias by purposively sampling ten participants and their caregivers (including people across the range of ability levels of intellectual disabilities and paid and family caregivers) who had baseline assessments during the first 3 months of recruitment (maximum variance sampling). For the second group, we will also attempt to recruit ten Down syndrome and caregiver dyads who did not take up the invitation to participate in the pilot RCT. We will attempt to recruit people with family caregivers, people with paid caregivers and people across the range of ability levels of people with intellectual disabilities, but we acknowledge that there may in limitations in how successful we will be with this second group.

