**Methods/Design:**

TOP-COG is a feasibility and pilot double-blind randomized controlled trial (RCT), with a nested qualitative study, conducted in the general community. About 60 Down syndrome adults, aged ≥50 will be included. The intervention is oral simvastatin 40mg at night for 12 months, versus placebo. The primary endpoint is recruitment and retention rates. Secondary endpoints are (1) tolerability and safety; (2) detection of the most sensitive neurocognitive instruments; (3) perceptions of Down syndrome adults and caregivers on whether to participate, and assessment experiences; (4) distributions of cognitive decline, adaptive behavior, general health/quality of life, service use, caregiver strain, and sample size implications; (5) whether Aβ42/Aβ40 is a cognitive decline biomarker. We will describe percentages recruited from each source, the number of contacts to achieve this, plus recruitment rate by general population size. We will calculate summary statistics with 90% confidence limits where appropriate, for each study outcome as a whole, by treatment group and in relation to baseline age, cognitive function, cholesterol and other characteristics. Changes over time will be summarized graphically. The sample size for a definitive RCT will be estimated under alternative assumptions.

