### Research questions

The research questions we will seek to answer are listed below.

1. What are the trial recruitment and retention rates and recruitment sources?

2. What are the rates of tolerability and safety of simvastatin 40 mg OD?

3. Which instruments are the most sensitive for detecting early cognitive decline with the least floor effect in adults with Down syndrome adults?

4. What are the perceptions of adults with Down syndrome and their caregivers regarding their decision whether to participate and be randomized and their assessment experiences?

5. What are the distributions of the primary outcome measure (cognitive decline) and key secondary outcome measures (adaptive behavior, general health and quality of life, service use and caregiver strain) that would be used in a definitive RCT, and what are the sample size implications of these distributions?

6. Is Aβ42/Aβ40 a biomarker for cognitive decline?

7. Do the results support proceeding to a full RCT?

The outcome measures we will use to answer each of the research questions listed above are described in the subsections that follow.

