#### Research question 1: feasibility

1. The numbers screened and recruited each month over the course of the recruitment period

2. A measure of the retention of participants in the study after 12 months

3. The percentage of the total number of participants recruited from each source and the number of contacts with each source to achieve this (The source will be identified during the initial telephone call to assess suitability of inviting the person to participate. Each contact made will be recorded by the researcher and Scottish Primary Care Research Network staff documenting each contact on a contact recording sheet.)

4. The number of participants recruited per base general population size.

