### Statistical power

Approximately 60 participants with Down syndrome ages 50 and older will be randomized. Recruitment feasibility will be assessed on the bases of the number of people identified per 10,000 population and the percentages of those contacted who would like to participate, and, among those, the percentage who are eligible to participate. For example, if 200 individuals are contacted and 100 agree to be screened, from among whom 60 are eligible for randomization, then the overall recruitment rate will be 30% with a 90% confidence interval (CI) of 25% to 36%. This will be sufficiently accurate to allow planning for a larger RCT. Similarly, if 50 participants complete the 12-month follow-up, the retention rate will be 83% with a 90% CI of 73% to 91%.

The variance of the rate of cognitive decline will be estimated to calculate the sample size required for a definitive RCT. The precision of this estimate is a function of the sample size in this pilot study. We think that a sample size of 50 participants from whom we gather 12-month outcome data is appropriate at this stage to provide a variance estimate that is reasonably precise, without requiring that we recruit an excessively large sample. With 50 participants, a 90% CI for the variance in the rate of cognitive decline will have a width of approximately 70% of the estimated variance. A smaller sample size in this pilot study would greatly increase the uncertainty in the variance estimate, whereas calculation of a more precise estimate could require considerably more participants. For example, halving the width of the 90% CI for the estimated variance would require 180 participants, which we believe is too large for a pilot study designed to show the feasibility of an RCT.

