### Data analysis

#### Recruitment

During the initial phone call, we will identify the source to which the person responded. We will describe the percentage of the total recruited from each source and the number of contacts with each source required to achieve this total (via diary records). We will also calculate recruitment by base general population size.

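### Yield by recruitment source may be misattributed, because source is taken only from what repliers know on the screening call

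*Protocol article*

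**What the plan says.** The Abstract of the protocol article states: "The primary endpoint is recruitment and retention rates". Under Research questions, the first question is wider: "What are the trial recruitment and retention rates and recruitment sources". The section Research question 1: feasibility then lists, as a separate measure, "The percentage of the total number of participants recruited from each source and the number of contacts with each source to achieve this".

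Two kinds of record feed that measure.

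- **Effort by source** is logged by staff: "Each contact made will be recorded by the researcher and Scottish Primary Care Research Network staff documenting each contact on a contact recording sheet".
- **Source of each recruit** is established on the first telephone call. Participants and their recruitment describes this: "we will inquire if the person knows the source of the information pack they received". The Recruitment paragraph of Data analysis repeats the method and gives the output: "We will describe the percentage of the total recruited from each source".

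Participants and their recruitment lists six routes, with snow-balling, in the same three health board areas, and says that all older adults with Down syndrome are known to primary care. It also provides for high interest: "we will recruit the first 60 suitable participants while continuing to measure the response rate".

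Statistical power illustrates the overall recruitment rate with 200 individuals contacted, 100 agreeing to screening and 60 eligible, giving 30% with a 90% interval of 25% to 36%.

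**The concern.** Comparing routes is a stated purpose of the study: Study aims includes testing recruitment strategies to inform later trials in this population. A comparison of yield needs recruits by route as well as effort by route. Effort is logged as it happens. The recruits are assigned to routes afterwards, by what the person on the call happens to know, and the wording of the question itself allows that some will not know.

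Two features make this weak here. First, if every eligible person is known to primary care, anyone on a charity list, known to a specialist service or supported by a provider organisation could also be approached through primary care. A person reached twice has no single correct answer to the question. Second, the participants have intellectual disabilities and packs may be handed on, so neither participant nor caregiver need know who issued the pack.

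At stake is the advice to a full trial on which routes to fund. A route that people remember easily would look more productive than it was, and one that they forget or never knew would look less so.

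**Working it through.** **Inputs from the protocol article**

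- Overall example: 200 contacted, 60 eligible (Statistical power).
- About 60 randomised; six listed routes (Participants and their recruitment).
- Source asked on the telephone; contacts with each source logged by staff (Research question 1: feasibility; Data analysis, Recruitment).

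**Assumptions, not in the document**

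- Equal true yield across the six routes, ignoring snow-balling: 60/6 = 10 recruits per route.
- A share *u* of recruits cannot name the source, the same share for every route: 10%, 20% or 30%.

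**Step 1: the plan's own figure.** The exact (Clopper-Pearson) 90% interval for *x* of *n* runs from the 5% quantile of Beta(*x*, *n* − *x* + 1) to the 95% quantile of Beta(*x* + 1, *n* − *x*). For 60/200 = 30% it is 24.7% to 35.8%, which rounds to the stated 25% to 36%. The figure reproduces.

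**Step 2: does recall enter that figure?** Recruits named to the six routes, plus those with no known source, add to 60 whatever people recall. The rate stays at 60/200 = 30%. Recall error moves recruits between sources and leaves the total alone.

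**Step 3: sampling error of one route's share.** 10/60 = 16.7%, with an exact 90% interval of 9.3% to 26.6%.

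**Step 4: range added by unknown source.** Of the route's 10 recruits, 10(1 − *u*) name it, and 60*u* of all recruits name nothing. Without further information the share lies between:

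- lower bound = 10(1 − *u*)/60, if none of the unknowns came by this route;
- upper bound = [10(1 − *u*) + 60*u*]/60, if all of them did.

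| *u* | Unknown | Named to route | Lower bound | Upper bound |
|---|---|---|---|---|
| 10% | 6 | 9 | 9/60 = 15% | 15/60 = 25% |
| 20% | 12 | 8 | 8/60 = 13% | 20/60 = 33% |
| 30% | 18 | 7 | 7/60 = 12% | 25/60 = 42% |

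**Step 5: reading the table.** At 10% unknown the range lies inside the sampling interval of 9% to 27%. At 20% and 30% its upper end passes 27%; the lower end stays inside throughout. These are bounds, not expected errors. If not knowing is unrelated to route, the share among those who know is 8/48 = 16.7% at *u* = 20%, which is the true value. The distortion arises when knowledge differs by route. The table covers only people who give no answer. It does not cover people who name the wrong source, or who were reached by several.

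**The case against.** The strongest reply has three parts.

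**This is an article.** Pack coding, removal of duplicates and the handling of unknown answers may sit in the full protocol or the analysis plan, so their absence here proves nothing. That stands as far as it goes, and a reader should not conclude that no such step exists. But the point rests on a method that the article does state, in three places: source comes from the telephone call.

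**The contact sheets cover it.** They record effort by source, which is half of the yield. As described, they do not link a reply to a pack, so they do not settle attribution.

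**The output is only descriptive.** True, and source yield is not named in the Abstract's primary endpoint. That limits the weight of the point.

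A reader might go further and infer that the overall recruitment rate, and so the primary endpoint, is biased by recall, by duplicate contacts and by the cap at 60. The document does not support that.

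- *Recall* does not enter the rate (Step 2).
- *Duplicates:* Statistical power speaks of individuals contacted, not packs sent. One can suppose that 20% of 200 contacts were repeats and obtain 60/160 = 37.5%, or 10% and obtain 60/180 = 33%, but both proportions are invented, and the second result lies inside the stated interval.
- *Cap:* 60/300 = 20% would follow only if 60 randomised were divided by contacts that ran on to 300. The article nowhere proposes this. The cap applies only if interest is high, response is still measured after it, and screened and recruited numbers are reported monthly. What remains open is whether eligibility is still assessed after the 60th participant.

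**Conclusion.** The point holds for yield by source only. That measure depends on repliers knowing who issued their pack, in a population where the routes probably overlap, and it may be misattributed. The direction is unknown. As to size, with 10 recruits per route and 20% unable to name a source, a true share of 17% could not be placed more closely than 13% to 33%. The equal split and the 20% are assumptions. Overlap of actual mailings is inferred from the list of routes and the statement about primary care, not reported.

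The overall recruitment rate is not shown to be biased, and the 25% to 36% interval is correct for the example given. This is an inexpensive improvement to a secondary descriptive output of a feasibility trial, and no challenge to its primary result.

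**What to change.** - Print a source code on every information pack and reply slip, and log the number of packs issued by source. A code still identifies the issuing route when a pack is passed on.
- Keep the telephone question as back-up, and ask it so that every route that reached the person is recorded.
- Report yield by source with an explicit unknown/multiple category, instead of forcing each recruit into one route.
- State that the recruitment rate counts unique people contacted.
- If the cap of 60 is reached, compute the randomised/contacted rate on people contacted up to the 60th randomisation, and report later response separately. This is a clarification; monthly counts are already planned.

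The cost is coded stationery and a simple log, with no added visits or assessments. Packs already sent cannot be coded, and Trial status gives June 2014 for the end of recruitment, so part of the mailing may be past changing. The counting and reporting rules can still be applied to everyone, within what the existing contact records allow.

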### Inclusion and exclusion criteria

The inclusion criteria are (1) a diagnosis of Down syndrome and (2) age 50 years or older. The exclusion criteria are listed below:

1. No consent obtained

2. Unable to comply with the protocol, including providing blood or saliva for baseline ApoE e4 measurement and venous or capillary blood for cholesterol measurement

3. Dementia at baseline (as the study is investigating primary prevention)

4. Diabetes (as this is an indication for prescription of a statin)

5. Clinically evident atherosclerotic disease (as this is an indication for prescription of a statin)

6. Being at risk for cardiovascular disease (as this is an indication for prescription of a statin)

7. Liver disease

8. Chronic renal insufficiency

9. Currently being prescribed any of the following:

a. A statin

b. Fibrates

c. Nicotinic acid

d. Cyclosporine

e. Triazole antifungals, including fluconazole, itraconazole, posaconazole, ketoconazole, voriconazole, miconazole oral gel, verapamil)

f. Macrolide antibiotics (including erythromycin, clarithromycin, telithromycin)

g. Danazol

h. Fusidic acid

i. HIV protease inhibitors (for example, nelfinavir, nefazodone, verapamil, amiodarone, warfarin, diltiazem, amlodipine)

j. Moderate CYP3A4 inhibitors (if the person lives alone or has only part-time paid support)

k. Hepatitis C protease inhibitors (for example, boceprevir, telaprevir)

10. Previous serious adverse reaction to a statin

11. Unable or unwilling to avoid consumption of grapefruit juice

12. Excessive alcohol use (defined as >21 U/wk for men and >14 U/wk for women)

### Group allocation and blinding

Participants will be randomly assigned to either simvastatin or placebo and stratified by age, ApoE e4 allele and cholesterol level. After collecting baseline data and samples, the researcher will notify the Robertson Centre for Biostatistics (RCB) of the participant’s study number and age via the web portal. The laboratory will notify the RCB of the participant’s ApoE status and cholesterol level, also via the web portal. The RCB will then notify the pharmacy of group allocation and generate an email to the research assistant notifying him or her that randomization has taken place as well as of the medication pack number assigned. The pharmacy will then dispense the medication. A verifiable audit trail will be ensured. The research assistant will telephone participants to check whether the medication has arrived and instructions are fully understood. The research team will therefore remain blinded to both ApoE and group allocation status, as will the participants and their caregivers. Medications will be dispensed within 4 weeks of baseline data collection. This time frame will allow for batching of the ApoE analyses.

### Duration of participation

#### Participation

Each participant’s participation in the study will last for 12 months postrandomization unless they withdraw prematurely.

#### Completion

The date of completion for safety is defined as the last dose of simvastatin or placebo plus 30 days. For other study outcomes, each participant will be considered to have completed the study either after the completion of the last assessment visit or after receiving the last dose of simvastatin or placebo, whichever is later. The date of discontinuation will be recorded as the date on which a participant and/or investigator determines that the participant can no longer comply with the requirements for any further study visits or assessments.

### Assessments

Assessments and blood tests will be conducted either in the person’s own home or at another venue if the participant/caregiver prefers. Home visits will be offered in order to increase recruitment and retention and for the convenience of the participants and caregivers, as well as to conduct the psychometric tests as accurately as possible by conducting them in a familiar, comfortable environment for the participant.

### Intervention

The intervention is simvastatin 40 mg at night by oral administration. The simvastatin will be overencapsulated. The control group will receive an oral placebo capsule at night by mouth. The capsules are to be swallowed whole, not chewed. Dose modifications are not allowed. A summary of product characteristics is available, as is an Investigational Medicinal Product Dossier. The drug and placebo will be prepared by the Pharmacy Production Unit based at the Western Infirmary in Glasgow.

#### Unblinding procedure

Unblinding will be permitted in emergencies where, for medical or safety reasons, it is necessary to know which treatment a participant has received. Study participants will be provided with a Participant Alert Card that will include the name of the investigational study drug, their study number, the investigator’s name and a 24-hour telephone number for unblinding purposes. Unblinding will be done via a telephone menu system. Several prompts in the system will warn the user that he or she is required to be a health professional and that name and other pertinent information must be recorded. At each unblinding, an email alert to the Chief Investigator will be generated. Requests will be set at a maximum of two per 24 hours to prevent malicious unblinding. The Participant Alert Card will be collected from participants at the end of their involvement in the study.

#### Expected adverse reactions

The expected adverse reactions are listed below. There is no theoretical reason to expect a higher rate in adults with Down syndrome.

1. Myalgia

2. Myositis

3. Rhabdomyolysis

4. Flulike symptoms

5. Fatigue

6. Headache

7. Nausea

8. Diarrhea

9. Fatal and nonfatal hepatic failure

10. Raised HbA1c and fasting glucose

11. Diabetes mellitus

12. Cognitive impairment (rarely)

#### Definitions of muscular adverse reactions

1. Alanine aminotransferase and aspartate aminotransferase elevation will be defined as more than three times the upper limit of normal.

2. Myalgia is defined as muscle ache or weakness without creatine kinase (CK) elevation.

3. Myositis is defined as muscular symptoms with a CK level more than ten times the upper limit of normal.

4. Rhabdomyolysis is defined as a CK level >10,000 U/L with or without muscular symptoms.

All AEs and intercurrent illnesses will be recorded, notified, reported, analyzed and managed in accordance with the CTR. The research sponsor’s standard operating procedures for recording and reporting AEs and serious AEs will be followed. An annual safety report will be submitted to the Medicine and Healthcare Products Regulatory Agency and the REC within 60 days of the anniversary of the issue of the clinical trial’s authorization. Safety data will be measured through three monthly telephone interviews.

